## Abstract

**Background:**

There is high prevalence of prediabetes and type 2 diabetes mellitus (T2DM) in Saudi Arabia that is still increasing. Early diagnosis of prediabetes, and immediate, effective intervention is yet unestablished. Conventional health promotion approaches are used to educate prediabetic patients. Behavior modification is very effective in prediabetics to delay T2DM. Thus, the main objective of this study is to examine the effect of the new behavioral model, the Transtheoretical Model short messages (text 4 change) to modify lifestyle to prevent or delay the onset of T2DM, through promotion of a healthy diet and increased physical activity, in impaired glucose tolerance patients. Another objective is to estimate the impact of this model on markers of cardiovascular and metabolic risks as T2DM is one of the modifiable risk factors to prevent cardiovascular diseases.

**Methods:**

This is a randomized controlled trial. One thousand and sixteen, eligible Saudi adults will be recruited from the Heart Health Promotion study (HHP), which was conducted at the King Saud University from July 2013 to April 2014. These adults were at a higher risk of developing T2DM within 2–3 years. The research team’s database has a contact list and they will recruit individuals over 6–8 weeks. All participants will be randomized at a 1:1 ratio into two groups, receive group education about lifestyle modifications and written information about diet and physical activity. Text 4 change SMS texts will be sent only to the intervention group. All participants will be assessed at baseline, 6, 12, 18, 24, 30, and 36 months for behavioral change using a World Health Organization (WHO) STEPS questionnaire and for glycated hemoglobin, biochemical and anthropometric measurements using standard methods.

**Discussion:**

This new approach for promoting the importance of behavior modification in prediabetics is expected to delay and/or prevent the development of T2DM in Saudi Arabia, subsequently reducing the risk of cardiovascular morbidity and mortality too. Results from this study will promote an innovative and high-tech way to decrease the burden of cardiovascular diseases in Saudi Arabia.

**Trial registration:**

International Standard Randomized Control Trial, registration number ISRCTN10857643. Registered 4 June, 2018.

## Background

Impaired glucose tolerance (IGT) and impaired fasting glucose (IFG) are intermediate conditions sometimes called prediabetes, where blood glucose levels are above normal but below diabetic thresholds [1]. Seventy percent of individuals with prediabetes eventually develop type 2 diabetes mellitus (T2DM) [2]. While people with IFG have a 20–30% chance of developing diabetes over the course of 5–10 years [3–5], this chance escalates to 90% if the individual is diagnosed with IGT [6]. In Saudi Arabia, the prevalence of both prediabetes and T2DM is high (18.3 and 11.9%, respectively) and increases with age [7]. Even though T2DM is treatable, it is usually associated with other comorbidities such as hypertension, hypercholesterolemia and obesity. These conditions in patients with T2DM contribute to the development of cardiovascular diseases (CVD). Thus, T2DM is one of the modifiable risk factors that can decrease the risk of several chronic diseases such as CVD, and reduce its associated mortalities. A population-based study from England showed that prediabetes may convert back to normal glycemia [8]. Furthermore, landmark clinical trials have proven the effectiveness of lifestyle interventions towards a healthy diet and sufficient physical activity to reduce or delay the occurrence of T2DM by 50% in prediabetic individuals [9–11]. The Center For Disease Control and Prevention (CDC), and the American College of Sports Medicine have demonstrated that accumulation of 10,000 steps per day on most days of the week is an important component of improving glycemic control, insulin sensitivity, and/or cardiovascular (CV) risk in patients with T2DM [1, 12].

Targeting this at risk population of prediabetics and increasing their awareness about the importance of a healthy lifestyle will help in the long run, to significantly decrease the prevalence of T2DM in Saudi Arabia. While many educational programs have been used to promote health in the Saudi community, the use of a digital approach is still in its early stages [7]. Nowadays, the daily use of smartphones is vital due to their efficiency, connectivity and functionality. This makes the delivery of educational messages easier and more convenient.

Prediabetes complications have been associated with the long-term burden of CVD, which is a major cause of death among diabetic patients [13, 14]. The risk of developing CVD increased 2–4 fold compared to age-sex matched patients without diabetes [15]. Worldwide, 43% of diabetes patients are more likely to die prematurely, and the rate of these deaths was higher in developing countries compared to developed countries [16]. Diabetes has a negative impact on the individuals’ productivity and quality of life [17]. Diabetes also places a heavy economic burden on individuals, families, societies and countries. For example, globally, in 2017 diabetes consumed USD 727 billion from the health expenditure. In 2014, 14% of the total health expenditure of Saudi Arabia was utilized for diabetes management [18]. Recent studies showed that the prevalence of prediabetes among the general population in Saudi Arabia was 25.5% in 2014 [19], and 27% among university employees and their families in 2016 [20].

The 2018–2020 National Transformation Program delivery plan, one of the Kingdom’s Vision 2030 programs, aims to improve health outcomes through e-Health. Over the last decade, the mobile phone short message service (SMS) has been increasingly used to deliver interventions designed to enhance healthy behavior [21]. SMS messages have the advantage of being inexpensive, convenient, reach the intended person instantly, and can be tailored to the individual [22]. In Saudi Arabia, the mobile phone market witnessed the fastest growth in the Middle East region with 23 million smartphones in use in 2017 [23].

Theory-led interventions base components of a health intervention on behavioral change, this theory has been constructed and called ‘the Transtheoretical Model (TTM)’ [24]. TTM has been used to improve adherence to medications in patients with CV risk factors [25, 26], and to prevent or delay the onset of T2DM in people with IGT [27, 28]. It has also been used effectively to predict or measure behavioral change in eating habits [29] and physical activity [30].

TTM posits that behavior change passes through five stages, which are precontemplation, contemplation, preparation, action, and maintenance (Table 1**)**. These stages indicate the individuals’ willingness to change their behavior ranging from long-term inactive (i.e. precontemplation stage) to long-term active (i.e. maintenance) behavior. Each stage has processes of change that are methods to move an individual from one stage of behavior to the other (Table 2) [24]. For example, raising consciousness (a process of change) is more effective with an individual in the precontemplation and contemplation stages rather than a person in the maintenance stage. Consequently, tailoring interventional messages based on the individual’s stage of change would be more effective in progressing them to the next stage of change [32].

**Table 1 Tab1:** Stages of change with brief descriptions

Stage of change	Description
Precontemplation (PC)	The individual is not willing to change in the foreseeable future (measured as the next 6 months). Individuals in this stage are mostly uninformed or demoralized.
Contemplation (C)	The individual is willing to change in the next 6 months. Individuals in this stage are aware of some pros of behavior change but are still more inclined to value the cons.
Preparation (P)	The individual is willing to change in the foreseeable future (measured as the next month) and has already taken some small steps towards change (in the past year). Individuals in this stage usually have some plan on how to tackle this inactiveness.
Action (A)	The individual has changed, but not longer than 6 months. Individuals in this stage have ‘changed’ but have not reached the duration which exemplifies real behavior change.
Maintenance (M)	The individual has changed, longer than 6 months. Individuals in this stage have changed and are working not to relapse.
Adapted from open access of reference [31]

**Table 2 Tab2:** Processes of change in terms of experimental and behavioral processes (a brief description)

Process	Description	
Experiential processes		
Consciousness raising (CR)	The individual seeks increased knowledge about the causes, consequences and cures for their problem behavior.	From precontemplation to contemplation
Dramatic relief (DR)	The individual’s emotions about the problem behavior and possible solutions are evoked.	
Environmental reevaluation (ER)	The impact that the individual’s problem behavior has on their environment is reevaluated.	
Social liberation (SOL)	Attempts are made to increase alternatives for the individual’s former problem behavior.	
Self-reevaluation (SR)	Cognitions and emotions regarding the individual with respect to their problem behavior are reevaluated.	From contemplation to preparation and action
Behavioral processes		
Self-liberation (SEL)	The individual has the belief that he can change and commits to it by choosing a course of action.	
Helping relationships (HR)	The individual seeks trust and open discussion about the problem behavior as well as support for the healthy behavior change.	Action to maintenance
Counter-conditioning (CC)	The individual substitutes positive behaviors for the individual’s problem behavior.	
Reinforcement management (RM)	Steps or changes made by the individual are rewarded when in a positive direction or punished when in a negative direction.	
Stimulus control (SC)	Stimuli that may cue a lapse back to the problem behavior are avoided and prompts for healthier alternatives are inserted.	
Adapted from reference [31]		

Therefore, this study aims to examine the effect of an interventional TTM based on short messages (text 4 change) of lifestyle modification to prevent or delay the onset of T2DM. The intervention will promote a healthy diet and increased physical activity among subjects with IGT. The design for this trial is parallel groups, the allocation ratio will be 1:1, and superiority framework.

### Primary objective

To examine the effect of the TTM short messages (text 4 change) to modify lifestyle to prevent or delay the onset of T2DM, through promoting a healthy diet and increased physical activity among subjects with IGT.

### Secondary objectives

To estimate the impact of the TTM-based SMS messages (text 4 change) on regulating the level of biomarkers for cardiovascular and metabolic risks, lowering the indices of general and central obesity, and maintaining body measurements among nonobese individuals. To estimate the impact of the intervention program on the incidence of myocardial infarction, stroke, death and hospitalization. To examine the acceptability of the text 4 change motivational SMS messages among the intervention group.

## Methods/design

### Study design (setting, eligibility and recruitment)

This is a three-year randomized controlled trial that includes Saudis ≥18 years of age. Participants for the present study will be recruited from the Heart Health Promotion study (HHP), which was conducted at King Saud University from 8 July, 2013 to 30 April, 2014 [20]. In the HHP study, participants were recruited from the three primary health care clinics serving the employees and their families at King Khalid University Hospital [20]. The HHP study was conducted on a large group of Saudi adults, who were at a higher risk of developing T2DM within 2–3 years. Recent data record updates of the original study on May 2017, revealed that out of the total sample (1234 prediabetic subjects) enrolled in the HHP study, 218 individuals had developed overt diabetes during the last 4 years (May 2013–May 2017). Therefore, 1016 are eligible for the present study.

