### Inclusion criteria

The inclusion criteria for participants is Saudi adults aged ≥18 years, literate, prediabetic, with no contraindication of physical activity, have a smartphone with easy access to the internet and are willing and able to provide written informed consent to participate in the study.

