### Exclusion criteria

The exclusion criteria for participants is pregnancy, individuals who do physical exercise > 50 min/week, follow a diet regimen, have a history of myocardial infarction, have impaired renal function, and are diabetic.

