### Recruitment

Recruitment will take place over a 2-month period in order to ensure that all eligible subjects (from the HHP study) who fulfil the inclusion criteria are invited, give consent, and are enrolled following the steps of the baseline visits as shown in the flowchart (Fig. 1). The research team’s database has a contact list and they will recruit individuals over 6–8 weeks. Subsequently, they will be given a 6-month follow-up visit appointment.

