### Randomization and blinding

Recruited, eligible participants will be randomized into two groups (1:1 ratio), using random numbers table generated in the Statistical Package for Social Studies (SPSS v. 21) (SPSS v. 21, IBM Corp., New York, NY, USA) by an independent statistician. The laboratory staff, biostatistician, health educator, and principal investigator will be blinded to the participant’s group allocation until the end of the study. The participants will not be blinded to the intervention due to its nature, as well as the research assistant/project manager who is responsible for disseminating the text message intervention.

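### Relatives from the same household can be randomised to opposite arms, which could expose controls to the messages and bias the comparison toward no effect

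*Protocol article*

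**What the plan says.** The section on study design, eligibility and recruitment describes the source: "participants were recruited from the three primary health care clinics serving the employees and their families". The Background points the same way, giving a prediabetes prevalence of "27% among university employees and their families in 2016" from the HHP reference.

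The Recruitment section aims to ensure that "all eligible subjects (from the HHP study) who fulfil the inclusion criteria are invited". The criteria concern the individual only. Inclusion begins with "Saudi adults aged ≥18 years, literate, prediabetic, with no contraindication of physical activity" and adds a smartphone and consent. Exclusion begins with "The exclusion criteria for participants is pregnancy, individuals who do physical exercise > 50 min/week, follow a diet regimen" and continues with medical history. Neither list mentions a relative who is already enrolled.

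Allocation is by person: "Recruited, eligible participants will be randomized into two groups (1:1 ratio), using random numbers table". The Lifestyle education section assigns each participant from a computer-generated list after consent. Both arms receive the same baseline package, and the phone messages are the only planned difference between them. Participants are not blinded. The same section bars further personal lifestyle advice to either group after baseline, except in reply to queries, but does not deal with relatives in opposite arms.

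**The concern.** Three stated features meet here: a source population that includes families, eligibility open to several members of one household, and randomisation of individuals. Together they allow one spouse to receive the messages while the other is a control.

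The intervention is information sent to a phone, and half of it concerns diet. The Healthy eating section lists less fast food, fat, salt and sugary drinks and fewer late-night snacks, which are choices that people who live together often make together. A control who sees the messages, or eats differently because a relative does, moves toward the intervention arm on both parts of the primary outcome (lifestyle behaviour and T2DM incidence).

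Intention-to-treat analysis keeps people in their assigned arms and does not remove this bias. If household membership is not recorded, a null result could not later be separated from contamination.

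**Working it through.** **Inputs from the Sample size calculation section.** Alpha 0.05 (two-sided assumed, because that reproduces the stated figure); power 80%; hazard 0.10 in the control arm and 0.07 in the intervention arm; minimum total 256 (128 per arm), raised to 300 for loss to follow-up. Nothing is added for contamination.

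**Step 1: reproduce 256.** For a two-sample exponential hazard-difference test with 1:1 allocation and no censoring, where λ̄ is the mean of the two hazards:

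N = [1.96 × √(4λ̄²) + 0.8416 × √(2(λc² + λi²))]² / (λc − λi)²

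With λc = 0.10, λi = 0.07 and λ̄ = 0.085: N = [1.96 × 0.170 + 0.8416 × 0.1726]² / 0.03² = 254.4, or 256 with equal arms. The stated figure is reproduced. I use the formula only to measure relative change. Whether it suits this trial is a separate question.

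**Step 2: how often pairs are split.** With 150 of 300 in each arm, the chance that a given person's relative falls in the other arm is 150/299 = 50.2%. If a share f of participants has one co-enrolled relative, the share of controls with an intervention relative is h ≈ f/2.

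**Step 3: dilution.** Let c be the share of the effect that passes to an exposed control. The control hazard becomes λc = 0.10 − h × c × 0.03. For h = 10% and c = 50% this is 0.0985, the hazard ratio is 0.07/0.0985 = 0.711, and

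N = [1.96 × 0.1685 + 0.8416 × 0.1709]² / 0.0285² ≈ 277.

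Power at 256 comes from the same formula solved for power. The values of h and c are assumptions, because the article gives neither.

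| h (controls exposed) | c (effect passed on) | Control hazard | Hazard ratio | Required total | Power at 256 |
|---|---|---|---|---|---|
| 5% | 25% | 0.0996 | 0.703 | 260 | 79.4% |
| 5% | 50% | 0.0993 | 0.705 | 266 | 78.6% |
| 10% | 50% | 0.0985 | 0.711 | 277 | 76.9% |
| 20% | 50% | 0.0970 | 0.722 | 303 | 73.2% |
| 10% | 100% | 0.0970 | 0.722 | 303 | 73.2% |
| 20% | 100% | 0.0940 | 0.745 | 369 | 64.7% |

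**Step 4: independence of relatives in the planned tests.** In the variance of the difference between arms, a correlated pair in the same arm adds a covariance term and a pair in opposite arms subtracts one. Under individual 1:1 allocation the two cases occur about equally often, so the terms roughly cancel. If whole households go to one arm, every pair is a same-arm pair and the terms no longer cancel.

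**The case against.** **Nothing shows that it will happen.** The article says whom the clinics serve. It does not say that couples were recruited or that anyone will share messages. A reader might infer that control relatives do receive the intervention at home and that the effect is diluted. The documents do not support that; they support only that the design permits it. This part of the objection stands.

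**Co-enrolment may be rare.** If 300 are taken from 1,016 and relatives enrol independently (an assumption), an eligible relative also enrols with probability 299/1015 = 29%. Then h = 10% (f = 20%) needs 0.20/0.295 = 68% of the pool to have an eligible HHP relative. With one relative each, h = 20% (f = 40%) would need 136%, which is impossible. The upper rows therefore require families to enrol together, or recruitment of all 1,016, which the Abstract describes. Both are possible, but neither is established.

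**Transfer is probably partial.** Messages are matched to the recipient's own stage of change and are sent only in the first 6 months. Of the 382 messages in Table 3, 193 concern physical activity, which does not act through shared meals. Controls already have the baseline education. A reader might use the short-cut 1/(1 − h)² with full transfer and obtain inflations of 1.23 (h = 10%) and 1.56 (h = 20%). Under the same full transfer, the formula that reproduces 256 gives 303/254.4 = 1.19 and 369/254.4 = 1.45. At half transfer with 10% exposed the increase is 277/256 = 1.08.

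**The article is condensed.** A household rule may stand in the full protocol, and if so the point falls away. But the article does state the eligibility criteria, the invitation rule and the unit of allocation, and the concern arises from those as stated.

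**The planned analysis.** A reader might also infer that the chi-square, t, log-rank and Cox analyses are invalid because relatives are correlated. Step 4 of the working shows that this has little force under individual randomisation.

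**Conclusion.** The point holds as a conditional weakness of the stated allocation rule. Where relatives are co-enrolled, about half of the pairs would be split, and any sharing would bias the behaviour and T2DM comparisons toward no effect. The direction is clear if sharing occurs; the size cannot be fixed from the article. If 5% to 20% of controls are exposed and half of the effect passes on, the required total rises from 256 to about 266 to 303, with power at 256 of about 79% to 73%. Full transfer with 10% exposed also gives about 303. If few relatives enrol, the loss is small. The analysis now planned is not in error on this account. The change is still worth making, because the bias is avoidable and can be prevented cheaply only before allocation.

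**What to change.** Before any allocation, ask each candidate whether another HHP invitee lives in the same household, and record the answer. The contact list may help, but the article does not say that it identifies households. Then adopt one of two rules in the randomisation text:

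- enrol one member per household; or
- obtain consent from all participating members first, then allocate the household by a single draw from the random list.

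The order in the second rule matters. Participants are unblinded, so a relative who consents after the household's draw could already know the arm, which would undermine allocation concealment.

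Under the second rule, use household-clustered (robust) variance in the Cox model and the other arm comparisons. Household allocation is what creates this need.

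Cost: one question at the baseline visit and a sentence each in the randomisation and analysis sections. The second rule brings a slight loss of precision, slight arm imbalance, and the work of completing household consent before the draw. The first rule gives up some eligible participants.

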### Inclusion criteria

The inclusion criteria for participants is Saudi adults aged ≥18 years, literate, prediabetic, with no contraindication of physical activity, have a smartphone with easy access to the internet and are willing and able to provide written informed consent to participate in the study.

### Exclusion criteria

The exclusion criteria for participants is pregnancy, individuals who do physical exercise > 50 min/week, follow a diet regimen, have a history of myocardial infarction, have impaired renal function, and are diabetic.

### Recruitment

Recruitment will take place over a 2-month period in order to ensure that all eligible subjects (from the HHP study) who fulfil the inclusion criteria are invited, give consent, and are enrolled following the steps of the baseline visits as shown in the flowchart (Fig. 1). The research team’s database has a contact list and they will recruit individuals over 6–8 weeks. Subsequently, they will be given a 6-month follow-up visit appointment.

